#### Children

Within each school, a RA met with participating children (individually or in small groups of a maximum of four children) in an available quiet room (e.g., school library) during a time that did not include any test or special activity. The RAs first informed children that their parent had agreed to participate in a study, without mentioning the parent’s participation to the parenting program. They then invited the children to fill out a questionnaire but specified that even though their parent gave them permission to participate, they could decide for themselves if they wished to participate or not. All children thus gave their verbal assent for their participation*.* Children completed paper-pencil questionnaires on their own but the RA remained available to answer questions about the questionnaire and study, if needed.

#### Group facilitators

Group facilitators audiotaped the sessions, answered a short questionnaire at the end of each session about the material covered, and monitored parents’ attendance. We also collected information about facilitators’ experience (in years), their age and sex, and whether they had children of their own to control for these factors, if needed. Each facilitator signed an informed consent form before providing this information.

### Distinguishing the program’s implementation from its evaluation

To reduce assessment bias, we ensured that parents made a clear distinction between the parenting program (which we called “the workshop”) and its evaluation (which we called “the study”). Second, we explained that compensation was contingent upon questionnaire completion, not on program participation. We also made this distinction salient by assigning different tasks to different members of our team. The research coordinator and RAs (rather than facilitators) took care of all research communication and procedures (i.e., questionnaires, consent forms, compensation) to foster role clarity. Group facilitators were asked to avoid talking about the study and to refer parents to the research coordinator if questions about the study arose.

### Instruments

#### Primary outcome

At each assessment time (pre-intervention, 1-week post-intervention, 6-month and 1-year follow-up), child’s mental health was assessed with different questionnaires via three different assessors (i.e., children themselves, their parent and their teachers). First, parents were asked to evaluate their child’s mental health using the two subscales - I and E problems - of the *Child Behavior Checklist* [52] (CBCL), a common outcome in trials assessing parenting programs. The CBCL is one of the most widely used validated instruments to assess children’s mental health. The E syndrome (Cronbach alphas T1/T2 = .88/.85 in our pilot study) reflects rule-breaking behavior and aggressive behavior whereas the I syndrome (Cronbach alphas T1/T2 = .81/.78 in our pilot study) reflects problems of anxiety/depression, withdrawal/depression and somatic complaints.

#### Secondary outcomes

##### Complementary measures of child mental health

Children were asked to evaluate their own well-being using measures of positive affect, life satisfaction and self-esteem. Children’s positive affect scale was assessed with an adapted scale [53] based on the *Positive and Negative Affect Schedule* (*PANAS) for children* [54, 55] and used in our pilot study [41]. This subscale includes ten positive emotion items, chosen for their simplicity. This French subscale showed good internal consistency in our pilot study (Cronbach alphas T1/T2 = .86/.88). Children’s self-esteem was measured with the *Rosenberg’s Self-Esteem Scale* [56, 57], one of the most widely-used measures to assess children’s global self-esteem. It assesses the extent to which children have a positive attitude toward themselves, and shows good construct and convergent validity [57] as well as good internal consistency (Cronbach alphas T1/T2 = .71/.83 in our pilot study). Finally, items about children’s life satisfaction were drawn from the French version of the *Satisfaction with Life Scale* [58, 59], a subscale which demonstrated good internal consistency (Cronbach alphas T1/T2 = .89/.93) in our pilot study.

Children’s mental health problems and socio-emotional strengths were also assessed by their current school teacher. Teachers were asked to fill-out the *Teacher-Child Rating Scale* [60] (TCRS). The problem subscales of the TCRS assess I (shy-anxious) and E (acting-out) problems whereas the socio-emotional subscales tap frustration tolerance, task orientation and social skills, important self-regulatory skills.

##### Parenting

The three dimensions of an optimal parenting style (structure, affiliation and AS) were assessed at each assessment time, by both parents and children, using scales drawn from well-validated parenting questionnaires, translated to French using back translation and adapted for children when needed.

Parents completed the Laxness subscale of the *Parenting Scale* [61] to rate how they generally behave toward their children, using bipolar items, where poles are anchored with a structured and a permissive stance. This subscale has been associated with observations of laxness (*r* = .61) and shown to identify mothers having difficulties in handling their children. The internal consistency of our French version was good (Cronbach alphas T1/T2 = .75/.72) in our pilot study.

Six items of the Laxness subscale of the *Parenting Scale* [61] were adapted to measure children’s perception of the extent to which their participating parent is permissive or setting limits. The internal consistency was close to satisfactory for this scale (Cronbach alphas T1/T2 = .57/.56) in the pilot study.

Ten items of the Care subscale of the *Parental Bonding Instrument* [62] were translated to measure parental care and involvement (vs. rejection). This instrument has been positively related to an observational measure of parental care [62]. The internal consistency of our French version was good (Cronbach alphas T1/T2 = .79/.77) in the pilot study.

The Care subscale of the *Parental Bonding Instrument* [62] was adapted to gather children’s perception of their participating parent’s care and involvement, contrasted with indifference and rejection, and its internal consistency was also good (Cronbach alphas T1/T2 = .76/.70).

The *Autonomy-Supportive Parenting Skill Scale* was designed within our pilot study [41]. Twelve autonomy-supportive skills taught in the How-to Parenting Program are contrasted with various controlling strategies parents typically use. Parents rated bipolar items, where one pole is anchored with an autonomy-supportive response and the other with a controlling reaction. The internal consistency was acceptable at T1 and good at T2 (Cronbach alphas T1/T2 = .64/.81) in the pilot study.

Parents also completed the *Parental Attitude Scale* [63] to rate their attitude toward AS and psychological control. This scale has predictive validity and has been associated with observational measures of autonomy-supportive and controlling behaviors [63]. In the pilot study, the French version showed good internal consistency (Cronbach alphas T1/T2 = .76/.73).

Children completed an adapted version of the *Perceived Parental Autonomy Support Scale* [31] to assess their perception of the extent to which their parent uses autonomy-supportive and controlling strategies. This scale has a sound factor structure, demonstrates convergent validity, and predicts psychological adjustment. In the pilot study, its internal consistency was good (Cronbach alphas T1/T2 = .70/.78).

##### Parental mental health

Parents were asked to assess their own mental health at each assessment time. Symptoms of anxiety and depression were measured with the *General Health Questionnaire* [64] while negative affect and guilt were measured with the negative affect subscale of the *PANAS* and the guilt subscale of the *PANAS-X* [54, 65]. Parents also assessed positive indicators of their mental health, by rating their positive affect (with the *PANAS* [54]), life satisfaction (with the *Satisfaction with Life Scale* [58, 59]), perceived competence (with the Competence subscale of the *Basic Need Satisfaction in Relationships Scale* [66]) and their self-esteem (with the *Rosenberg’s Self-Esteem Scale* [56]).

#### Potential covariates

At pre-intervention, parents provided demographic questions to determine their age, gender, education level, family income, marital status, first language, ethnicity and number of children. Parents also indicated their children’s age and gender, and evaluated their child’s temperament (*Children’s Behavior Questionnaire* [67]). The measures used in the present study are summarized in an additional table file [see Additional file 1].

### Retention promotion

A 20$ (CAN) compensation was offered to parents each time they completed a questionnaire. After each questionnaire, participating teachers received 10$ (CAN) and children received a gift-certificate of 10$ (CAN) from a popular bookstore. Group facilitators were not compensated for filling out their own short questionnaire but were paid for their work.

### Statistical methods

We will adopt an intent-to-treat approach [68] as this approach increases external and internal validity. Our data will also be hierarchical in nature; pre-intervention, post-intervention, 6-month and 1-year follow up measures will indeed be nested within each parent, who are nested within a parenting group. Accordingly, multivariate hierarchical linear modeling (HLM) analyses will be conducted to test our hypotheses; these analyses have the advantages of estimating error terms while taking into account the nested nature of the data and allow for missing data without decreasing power. Analyses will thus include all participants who completed at least one assessment, regardless of the number of sessions they attended (for the experimental groups).

To evaluate change over time, the four assessment points (pre-intervention, post-intervention, 6-month follow-up, and 1-year follow-up) will be treated as repeated measures to estimate change between each subsequent time points [69]. This approach is chosen because it allows rates of change to differ across time.

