#### Differentiation

While some participants in the experimental condition may have not fully engaged in the program, some parents in the wait-list condition might have gained access to some of the program’s content. Indeed, contamination was possible since we decided to randomly assign participants within each participating school. This procedure was chosen over a cluster randomized trial to avoid conflating our experimental manipulation with schools’ characteristics, such as their size, socio-economic status (SES), educational philosophy, and to remove this unexplained between-school variability from the between-group main effect, thereby increasing statistical power.

Because all parents in the study heard about the program during the information meeting (see Recruitment section below), some parents assigned to the wait-list condition may have decided to buy and read the book (and try some skills). However they could not take part in the program, which presumably fosters increased learning due to group participation (e.g., weekly sessions with facilitators and other parents, exercises, homework, discussion and modeling). To control for this potential confound, we asked parents in the wait-list condition whether they had bought and read the book. Finally, to ensure differentiation between the How-to Parenting Program and other interventions as well as between the experimental and the control conditions, parents in both conditions were asked to document any intervention and/or a therapeutic activity used for their family.

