### Sample size

The pilot study suggests that medium effects can be expected (i.e., Cohen’s d around.5) [48] and the primary focus of the present study pertains to cross-level interactions. Hox [49] suggests that these effects depend more strongly on the number of groups than on the total sample size. Tabachnick and Fidell [50] further suggest that sufficient power for cross-level effects is obtained when the number of groups is 20 or larger, whereas Paterson & Goldstein [51] recommend having at least 25 groups. Following these recommendations, our goal was to have 32 level-3 units (parenting groups), 256 level-2 units (parents), and 1024 level-1 units (time points). Sufficient power was expected since this number of parenting groups is above the recommended threshold and allows for recruitment drawbacks.

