### Recruitment

The goal was to conduct the study within four grade schools per year, for 4 waves (recruiting about 64 parents to form 8 groups at each wave; see Flowchart in Fig. 1). The RCT began after obtaining ethics approval and funding. We first sought approval from three school boards, a prerequisite for soliciting school principals. We then sent information to school principals by mail at the beginning of each wave (September), who could contact the research coordinator for further information if they were interested in this program implementation and evaluation. There was no inclusion or exclusion criterion for school recruitment; all schools were invited. Given that we did not target specific types of schools nor SES neighborhoods, school participation first depended on school principals’ interest. When a school principal was interested in our study, information was given to all families by sending an information flyer via children’s schoolbag, in December. Parents then communicated their interest in the program by returning the flyer’s response section (reply slip). We asked teachers to refrain from recommending the parenting program to certain parents, to highlight its universal and voluntary nature. Recruitment thus also depended on each particular school’s general level of parental interest since the next recruitment stage (information meeting) could take place solely in schools in which a large number of parents returned their reply slip.

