### Consent and allocation

Information meetings for parents were held in schools in January. One of the principal investigators met with interested parents to provide them with information about the parenting program and its assessment. Parents were thus informed about the How-to Parenting Program, the random assignment, their voluntary participation as well as that of their participating child and his/her teachers. Parental consent forms were filled out at the end of that information meeting. This consent form comprises three distinct sections, allowing parents to give their consent (or not) separately for (a) their child’s participation, (b) their child’s teachers’ participation and (c) their own.

Random assignment of families was made after parents’ T1 questionnaires were collected, within each school. The research coordinator extensively shuffled the sealed anonymous envelopes containing T1 questionnaires before randomly assigning them in one of the two conditions. Next, parents received a phone call informing them of the group they were assigned to (either in the group beginning the following spring or in the group beginning during spring of the following school year; see Fig. 1 and Table 2).

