#### Primary analyses

The effect of the How-to Parenting Program will be evidenced by significant interactions between rates of change and experimental conditions. These interactions should reveal that child mental health increases over time for participants in the experimental condition, but not for participants in the control condition. Based on our pilot study, we expect that the program will be effective to decrease parent-reported I and E problems.

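### The stated model has no school term although families were randomised within school, so the power gain claimed for that design is not secured; the primary test loses precision only if schools differ in change over time

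*Protocol article*

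**What the plan says.** Under Consent and allocation, random assignment took place after parents' "T1 questionnaires were collected, within each school". The Differentiation section explains why this was preferred to a cluster randomised trial, at the price of possible contamination. One reason is to avoid conflating the intervention with school characteristics. The other is "to remove this unexplained between-school variability from the between-group main effect, thereby increasing statistical power".

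The Statistical methods section gives the hierarchy: "follow up measures will indeed be nested within each parent, who are nested within a parenting group". Sample size repeats the same three levels: "our goal was to have 32 level-3 units (parenting groups), 256 level-2 units (parents), and 1024 level-1 units (time points". Neither section names school. Preliminary analyses admits covariates only where a baseline imbalance between conditions is found.

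The four assessments "will be treated as repeated measures to estimate change between each subsequent time points", and under Primary analyses, "The effect of the How-to Parenting Program will be evidenced by significant interactions between rates of change and experimental conditions". Recruitment plans "four grade schools per year, for 4 waves", "recruiting about 64 parents to form 8 groups at each wave".

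**The concern.** Randomising within a stratum improves precision only if the analysis uses the stratum. The planned numbers imply one experimental and one wait-list group per school. A random effect for parenting group, with no school term, absorbs what the two groups of a school share and counts it as independent error. The imbalance rule would not bring school in, because within-school allocation balances school by design.

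The Differentiation section therefore claims a benefit that the stated model does not deliver. At stake is power: reported standard errors can be wider than the design warrants, and the test can run below its nominal level.

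**Working it through.** **The plan's own figures.** 4 schools × 4 waves = 16 schools. 4 × 8 = 32 groups, or 2 per school. 64 / 8 = 8 parents per group. 4 × 64 = 256 parents. 256 × 4 = 1024 time points. The 32/256/1024 reproduce exactly. The article gives no intraclass correlation (ICC), within-parent correlation, random-slope structure or numerical power, so everything below rests on assumed values.

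**1. Between-group main effect.** Total variance is 1, with school variance s, group variance g = 0.01 (assumed) and p = 1 − s − g.
- SE without school = √[(2/16)(s + g + p/8)].
- SE with school = √[(2/16)(g + p/8)].

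| s | without | with | ratio |
|---|---|---|---|
| 0.01 | 0.134 (√0.0178) | 0.129 | 1.04 |
| 0.05 | 0.149 | 0.126 | 1.18 |
| 0.10 | 0.166 | 0.123 | 1.35 |

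The gain is lost here whenever s > 0.

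**2. Change by condition, school differences constant over time.** A constant school effect subtracts out of each parent's change. With within-parent correlation r = 0.6 (assumed), the variance of change is e = 2(1 − 0.6) = 0.8. The SE is √[(2/16)(0.8/8)] = 0.1118 with or without school, a ratio of 1.00 for any s. A small REML check (12 replicates per setting, some convergence warnings) agreed: 0.1127 in both models at s = 0.05, and 0.1093 in both at s = 0.10. A school intercept alone therefore does nothing for the primary test.

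**3. Change by condition, schools differing in change.** Let t be the school-by-time variance in change, assumed 0.01 to 0.05.
- Group-level random slopes: SE ratio = √[(t + 0.1)/0.1], which is √1.1 = 1.05 at t = 0.01 and √1.5 = 1.22 at t = 0.05.
- Group-level random intercepts only: t enters the residual and the ratio = √[(0.8 + t)/0.8], which is 1.01 and 1.03.

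**4. Effect on the test.** This is an analysis of group means, not the planned hierarchical model. Assumptions: 16 schools × 2 groups × 8 parents; school share s of the variance in change; group ICC 0.05 in the treated arm; d in SD units of change; two-sided 5% level.

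Per school, the contrast variance with school blocked is B = 0.05 + 2(1 − s)/8. With school ignored it is B + 2s.
- s = 0.02: B = 0.295; 0.335/0.295 = 1.14.
- s = 0.05: B = 0.2875; 0.3875/0.2875 = 1.35.
- s = 0.10: B = 0.275; 0.475/0.275 = 1.73 (1.74 if the treated-group variance is taken out of the residual rather than added).

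Simulation (40,000 trials per setting) compared a two-sample t-test on 32 group means with a t-test paired by school:

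| s | type I error, ignored | power at d = 0.5, ignored vs blocked | power at d = 0.3, ignored vs blocked |
|---|---|---|---|
| 0.02 | 3.8% | 93 vs 93% | 53 vs 55% |
| 0.05 | 2.4% | 91 vs 94% | 47 vs 56% |
| 0.10 | 1.1–1.4% | 86–87 vs 95% | 37 vs 58% |

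The Sample size section expects d around 0.5; d = 0.3 is shown only as a less favourable case. If schools do not differ in change (s = 0), blocking costs about 3 points at d = 0.3: 57% ignored against 54% blocked.

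**The case against.** The strongest reply is that the primary test is a within-parent change contrast. The school features named in the Differentiation section (size, socio-economic status, educational philosophy) are largely stable and cancel from it. That stands. A reader might infer that the primary standard errors are too wide as a matter of course; the article does not support this, because it says nothing about whether schools differ in change or whether group slopes are random. Such differences are plausible: schools join in different yearly waves, and the 6-month and 1-year assessments fall in the next school year. But they are not documented.

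A reader might also infer that contamination was accepted for nothing. That goes too far. Within-school allocation still separates the intervention from school characteristics, whatever model is fitted.

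Finally, this is a condensed article, and a fuller analysis plan might add a school term. That lowers confidence but does not remove the point. The article states the levels of the model twice and makes a power claim that those levels do not support, so the mismatch is in the text itself.

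**Conclusion.** The point holds in limited form. The article's reason for randomising within school and its stated model do not fit together. The loss is certain for a between-group main effect if school variance is above zero. For the primary change-by-condition test it is conditional: none if school differences are stable, about 1–3% on the SE with group random intercepts only, and about 5–22% with group random slopes, at an assumed school-by-time variance of 0.01 to 0.05.

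At the protocol's own effect size, the power loss in the group-mean analysis is about 0, 3 and 8 points for school shares of 2%, 5% and 10% of the variance in change. Nothing in the article shows that a share as high as 10% applies. The omission makes the test conservative; it does not bias the estimate in the balanced design or create false positives. It should be fixed, but it does not threaten the validity of a positive result.

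**What to change.** In Statistical methods, state that families were randomised within school, and include school and school by time in the primary model. Either enter them as fixed effects, or add a random level above parenting group with random time contrasts, so that condition by time is estimated within school. School also carries wave if each school takes part in one wave only. Fix the choice, and whether group-level slopes are random, before the data are analysed. If school is not to be modelled, limit the power claim in Differentiation accordingly.

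The cost is a line of specification, since school is known for every family. Fixed school effects use 16 − 1 = 15 degrees of freedom per time contrast. If schools do not in fact differ in change, about 3 points of power are lost at d = 0.3.

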#### Primary hypothesis

We expected that children of parents in experimental groups would experience fewer parent-reported I and E psychological problems over time whereas children of parents on the wait-list would not show improvements during that year (i.e., stable or increasing psychological problems).

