### Participant timeline

All parents and children completed their questionnaires before randomization (pre-intervention; T1), 1 week after the seven-week program (post-intervention; T2), and again at 6-month (T3) and 1-year (T4) follow-ups to assess change over time (see Table 2). Teachers each completed two questionnaires, since children’s teachers at the beginning of the study (T1 and T2, in February and April) were not the same teachers as during the last part of the study (T3 and T4, in October and April of the following school year).

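### The primary success rule rests on interactions with adjacent-interval changes without saying which decide, and the year-long arm difference is not itself a named test

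*Protocol article*

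**What the plan says.** All statements are in the protocol article.

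- **Hypothesis (Primary hypothesis).** Children in the experimental arm "would experience fewer parent-reported I and E psychological problems over time", whereas "children of parents on the wait-list would not show improvements during that year". The time frame is the year.
- **Assessments (Participant timeline).** Parents report at T1 before randomization, then "1 week after the seven-week program (post-intervention; T2), and again at 6-month (T3) and 1-year (T4) follow-ups".
- **Coding of time (Statistical methods).** The four assessments "will be treated as repeated measures to estimate change between each subsequent time points". The reason given is: "This approach is chosen because it allows rates of change to differ across time".
- **Success rule (Primary analyses).** The effect "will be evidenced by significant interactions between rates of change and experimental conditions". The text adds: "These interactions should reveal that child mental health increases over time for participants in the experimental condition, but not for participants in the control condition".
- **Expected shape (Pilot study).** Gains seen at post-intervention were still there 6 and 12 months later. The Discussion expects similar effects in this trial.

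Neither the primary analysis text nor the rest of the Statistical methods section names a T1-to-T4 contrast, an average over the post-baseline visits, or a joint test of condition by time.

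**The concern.** A separate rate for each interval gives three interactions per outcome: condition by (T2-T1), by (T3-T2) and by (T4-T3). The stated rule refers to them in the plural and stops there. It does not say whether one is enough, whether all are needed, or whether they are judged together.

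This matters because the adjacent terms and the hypothesis answer different questions. The arm difference at 6 months is the sum of the first two terms, and at 1 year the sum of all three. A benefit reached at T2 and then held leaves the second and third terms at zero. A benefit that builds slowly is split into thirds. A benefit that is lost still shows in the first term. With the deciding term left open, the choice could be made after the results are seen, and the answer on efficacy could depend on it.

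**Working it through.** **The plan's own figures.** 4 waves x 8 groups = 32 groups; 4 x 64 = 256 parents; 256 x 4 assessments = 1024 time points. All three match the Sample size section. No power or alpha is stated, so there is no power figure to reproduce.

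**Inputs.** From the article: 256 parents, two arms, and an effect of about d = 0.5, not tied to any interval. Assumed: 128 per arm, SD 1 at every visit, equal correlation r between visits (0.6, with range 0.5 to 0.8), two-sided 5%, no attrition, no clustering by parenting group.

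**Formulas.**
- Difference between arms in change over any two visits: SE = sqrt(2(1-r) x 2/n). At r = 0.6: sqrt(0.8 x 2/128) = 0.112.
- Mean of T2, T3, T4 minus T1: variance factor 1 + (1+2r)/3 - 2r = 0.533 at r = 0.6; SE = sqrt(0.533 x 2/128) = 0.0913.
- Power = Φ(|effect|/SE - 1.96), plus a negligible opposite tail unless the effect is near zero.
- Joint test: noncentral chi-square on 3 df.

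Examples at r = 0.6: 0.5/0.112 = 4.47, power 0.994; 0.25/0.112 = 2.24, power 0.609; 0.167/0.112 = 1.49, power 0.320.

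**Results at r = 0.6.** Effects are in SD units and positive values favour the programme.

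| True arm difference at T2, T3, T4 | True adjacent interactions | Power, adjacent tests | T4-T1 | Mean(T2-T4)-T1 | Joint 3 df |
|---|---|---|---|---|---|
| Early, kept: 0.5, 0.5, 0.5 | 0.5, 0, 0 | 99%, 5%, 5% | 99% | >99% | >99% |
| Gradual: 0.167, 0.333, 0.5 | 0.167 each | 32% each | 99% | 95% | 99% |
| Fades: 0.5, 0.25, 0 | 0.5, -0.25, -0.25 | 99%, 61%, 61% | 5% | 78% | >99% |

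For r from 0.5 to 0.8, each adjacent test in the gradual case has 27% to 56% power, against 98% or more for T4-T1. Each later term in the fading case has 52% to 88% power.

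**What the open rule implies.** Neighbouring interaction estimates correlate at -(1-r)/(2(1-r)) = -0.5 because they share a visit; the first and third are uncorrelated. Simulating three normal statistics with these correlations at r = 0.6 gives:
- *Any one suffices, no true effect:* at least one is significant in about 13% of trials per outcome (14.3% if they were independent, 1 - 0.95^3). Counting only results that favour the programme, it is about 7%, against 2.5% for a single test.
- *Any one suffices, benefit fades to zero:* a favourable term is significant about 99% of the time.
- *All three must favour the programme:* under the early, kept pattern this happens in fewer than 1 in 10,000 trials; under the gradual pattern in about 0.2% (about 8% at r = 0.8).

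**The case against.** The strongest reply is that the model is sound and only the reporting is loose. Much of this stands.

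- **A reader might infer that no planned test addresses the hypothesised effect.** The documents do not support that. The T1-T2 interaction detects an early benefit with full power (98% or more over the range of r), and an early benefit is what the pilot suggests. The T4-T1 effect is the sum of three coefficients already estimated. The wording does not exclude a joint condition-by-time test.
- **A reader might infer that maintenance cannot be told from fade-out.** It can. The later interactions test exactly that. In the fading case each has 61% power, and at least one is significantly adverse about 92% of the time at r = 0.6. The success rule also asks for a pattern of improvement over time, which a clear reversal would not fit.
- **The change of teacher between T2 and T3** might be raised too. It concerns secondary outcomes, is disclosed, and would affect T1-referenced contrasts at T3 and T4 just as much.
- **The phrase on successive time points is loose.** It could mean change from T1 to each later visit. The stated reason, that rates may differ across time, makes adjacent intervals the more natural reading.
- **An averaged contrast is not a 1-year test.** In the fading case its true value is 0.25 and it is significant 78% of the time.
- **A journal article may leave detail to an analysis plan that is not shown.** That would answer a mere omission. Here the article states a coding and an evidence rule, and the two together do not match the stated hypothesis.

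**Conclusion.** The concern holds in a limited form. Time is coded, on the natural reading, as adjacent-interval change; efficacy is to be shown by "significant interactions between rates of change and experimental conditions"; and the deciding interaction or number of interactions is not fixed. The year-long difference can be derived from the model but is not named as a test. Under the trial's own expected pattern, two of the three interactions are true nulls. Depending on how the rule is read, it is too lenient (about 13% false positives per outcome, with a faded benefit able to count) or nearly impossible to pass.

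The power figures rest on the assumed correlation, equal arms, no attrition and no clustering, so they are upper limits on power. Two conclusions do not depend on them: the later terms are zero under a maintained gain, and a significant adjacent term is neither necessary nor sufficient for a 1-year effect. This should be fixed. It is a fault in the decision rule, not in the model or the data.

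**What to change.** Keep the same model with time categorical, so that rates can still differ between intervals, but reference it to T1. Before analysis, name one primary condition contrast for each of the internalizing and externalizing outcomes:

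- T4-T1, if the claim is an effect at 1 year; or
- the mean of T2, T3 and T4 minus T1, or a joint condition-by-time test, if the claim is an effect over the year. Either of these can be significant when the benefit has gone by T4, so neither should be reported as a 1-year effect.

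Whichever is chosen, report T2-T1, T3-T1 and T4-T1 with confidence intervals. Keep the adjacent-interval changes as secondary tests of maintenance or fade-out.

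The cost is a re-parameterisation with no new data. The adjacent-interval p-values lose primary status.
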